#### Patient shedding criteria

Subjects with poor compliance during the trial, affecting the safety and efficacy evaluation.Subjects with serious adverse events, complications, or specific physiological changes, who are not suitable to continue the trial.Children for whom trial blindness is broken.Children who choose to withdraw from the trial.When combined drugs, especially the drugs that have a greater impact on the effectiveness and safety of the experimental drug.Cases who withdraw from the trial, are lost to follow-up, or who die for before completing treatment.Cases with insufficient data, affecting the evaluation of effectiveness and safety.

#### Suspension criteria

Severe adverse reactions during the medication.Major errors in the clinical trial plan making it difficult to evaluate the drug effect; or important deviations in implementation of the plan (e.g. blind bottom leakage, etc.), making it difficult to evaluate the drug effect.Decision to terminate the trial by the national regulatory agency, the Ministry of Science and Technology and other relevant project departments.

### Interventions

Both the experimental group and the control group will be treated with test drugs or placebo together with basic treatment.

#### Basic treatment

Oral rehydration treatment, dietary treatment, and drug treatment as specified in the guidelines.
Oral rehydration treatment: oral rehydration salt solution (Shanghai Johnson Pharmaceutical Co., Ltd.).Diet treatment: carbohydrates and vegetables. Fasting high-protein, high-fat, and high-calorie foods.Medication treatment: zinc supplementation (elemental zinc 20 mg/day for 10–14 days. Elemental zinc 20 mg is equivalent to 100 mg zinc sulfate and 140 mg zinc gluconate).

#### Test drugs

Experimental group 1: basic treatment + Gegen Qinlian decoction granules + Erbai drink placebo: Radix Puerariae lobatae (Ge Gen) 10 g, Radix Scutellariae (Huang Qin) 10 g, Rhizoma Coptidis (Huang Lian) 5 g, Radix Glycyrrhizae (Gan Cao) 5 g. (child’s dose, divided into three packets), orally in three times. Placebo (same taste and packaging as Erbai drink granules), children aged ≥ 6 months to ≤r1 year: 3/7 packs/time, three times a day orally; children aged > 1 year to ≤ 3 years: 1/2 pack/time, three times a day orally; children aged > 3 years to ≤ 5 years: 3/4 pack/time, three times a day orally; and children aged > 5 years to ≤ 14 years: 1 pack/time, three times a day orally.Experimental group 2: basic treatment + Erbai drink granules + Gegen Qinlian decoction placebo: Radix Paeoniae Alba (Bai Shao) 10 g, Rhizoma Atractylodis Macrocephalae (Bai Zhu)10 g, Radix scutellariae (Huang Qin) 10 g, Semen Coicis (Yi Yiren ) 10 g, Rhizoma Atractylodis (Cang Zhu) 5 g, Semen Plantaginis (Che Qianzi)10 g (child’s dose, divided into three packs) orally in three times. Placebo (taste and packaging same as Gegen Qinlian decoction granules), children aged ≥ 6 months to ≤ 1 year: 3/7 packs/time, three times a day orally; children aged > 1 year to ≤ 3 years: 1/2 pack/time, three times a day orally; children aged > 3 years to ≤ 5 years: 3/4 pack/time, three times a day orally; and children aged > 5 years to ≤ 14 years: 1 pack/time, three times a day orally.Control group: basic treatment + Erbai drink placebo + Gegen Qinlian decoction placebo: placebo (taste and packaging same as Erbai drink granules and Gegen Qinlian decoction granules), children aged ≥ 6 months to ≤ 1 year old: 3/7 packs/time, three times a day orally; children aged > 1 year to ≤ 3 years: 1/2 pack/time, three times a day orally; children aged > 3 years to ≤ 5 years: 3/4 pack/time, three times a day orally; and children aged > 5 years to ≤ 14 years: 1 pack/time, three times a day orally. Relevant antibiotics (ceftriaxone sodium for injection: 50 mg/kg/day, single intravenous infusion) can be added if required during the course of the illness, if there is an increase in the frequency of stools, a lack of improvement in stool characteristics, fever, increased proportion of neutrophils in the blood, increased CRP or procalcitonin, or increased routine white blood cell count in the stools.

One course of treatment for the above three groups will last 5 days, and one to two courses can be administered continuously. The specific observation time and related items are shown in Table 1.

**Table 1 Tab1:** Specific observation time and related items

Stage		Enrollment	Clinical observation time (days)									
**Date of visit**		**0**	**1**	**2**	**3**	**4**	**5**	**6**	**7**	**8**	**9**	**10**
**Case screening**		**√**										
**Sign informed consent**		**√**										
**Random entry group**		**√**										
**Delivery of test drugs**		**√**										
**CRF completed**		**√**	**√**	**√**	**√**	**√**	**√**	**√◎**	**√◎**	**√◎**	**√◎**	**√◎**
**Basic medical history**		**√**										
**General information**		**√**										
**General inspection items**	**Physical examination**	**√**	**√**	**√**	**√**		**√**	**√◎**	**√◎**	**√◎**	**√◎**	**√◎**
	**Routine blood test**	**√**	**◎**	**◎**	**√**	**◎**	**◎**	**√◎**	**√◎**	**√◎**	**√◎**	**√◎**
	**Procalcitonin**	**√**	**◎**	**◎**	**√**	**◎**	**√**	**◎**	**◎**	**◎**	**◎**	**◎**
	**C-reactive protein**	**√**	**◎**	**◎**		**◎**	**◎**	**√◎**	**√◎**	**√◎**	**√◎**	**√◎**
	**Electrocardiogram**	**√**					**√**	**√◎**	**√◎**	**√◎**	**√◎**	**√◎**
	**Liver and kidney function**	**√**					**√**	**√◎**	**√◎**	**√◎**	**√◎**	**√◎**
	**Electrolytes**	**√**					**√**					
	**Routine urine test**	**√**					**√**					
	**Routine stools**	**√**	**◎**	**◎**	**√**	**◎**	**√**	**√◎**	**√◎**	**√◎**	**√◎**	**√◎**
	**Stool culture (including drug sensitivity)**	**√**					**√**	**√◎**	**√◎**	**√◎**	**√◎**	**√◎**
**Stool characteristics**		**√**	**√**	**√**	**√**	**√**	**√**	**√◎**	**√◎**	**√◎**	**√◎**	**√◎**
**Stool frequency**		**√**	**√**	**√**	**√**	**√**	**√**	**√◎**	**√◎**	**√◎**	**√◎**	**√◎**
**Symptom evaluation**		**√**	**√**	**√**	**√**	**√**	**√**	**√◎**	**√◎**	**√◎**	**√◎**	**√◎**
**Temperature card**		**√**	**√**	**√**	**√**	**√**	**√**	**√◎**	**√◎**	**√◎**	**√◎**	**√◎**

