## Methods/design

### Study aim

We aim to use Erbai drink and Gegen Qinlian decoction combined with antibiotics as intervention methods to evaluate the clinical efficacy of TCM for the treatment of bacterial diarrhea in children. We will also formulate clinical programs and guidelines for the treatment of pediatric bacterial diarrhea using TCM, to provide clinical evidence for the use of TCM in reducing the use of antibiotics.Based on the evaluation of the clinical efficacy of the TCM preparations and their combined application, we aim to investigate the mechanism of TCM in alleviating antibiotic resistance and enhancing the sensitivity of pathogenic bacteria to antibiotics.We aim to monitor the incidence of clinical adverse events/reactions, general physical examination items, and laboratory parameters.

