### Study design

This randomized, double-blind, placebo-controlled clinical trial will compare two different TCM preparations with a blank control group. The trial design is shown in Fig. 1.

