#### Selection criteria

Age from 6 months to 14 years.Meet the Chinese and Western medicine diagnostic criteria, course of the disease within 2 weeks, and condition mild to moderate.White blood cell count in routine stool ≥ 5/high-power field (HPF), or increased procalcitonin, percentage of CRP or neutrophils, or total number of white blood cells in routine blood.Able to obtain consent from a guardian, fill in the informed consent form, and agree to participate (children > 8 years old should sign a consent form).

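### Test drugs scales the packs by age for the placebos only; followed as written, the pack pattern would unblind children aged 5 or under

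*Protocol article*

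**What the plan says.** The protocol article claims a double-blind, placebo-controlled design in the abstract and again under Study design: "This randomized, double-blind, placebo-controlled clinical trial will compare two different TCM preparations with a blank control group". Each child is given two products. An experimental arm pairs one active preparation with the placebo of the other; control receives both placebos.

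Test drugs sets out, arm by arm, what is taken:

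- Group 1 (active Gegen Qinlian granules): the ingredients, then a child's dose "divided into three packets), orally in three times. Placebo (same taste and packaging as Erbai drink granules". The four age bands follow the word placebo.
- Group 2 (active Erbai granules): the same structure, "divided into three packs) orally in three times. Placebo (taste and packaging same as Gegen Qinlian decoction granules", again with the age bands after the word placebo.
- Control: "placebo (taste and packaging same as Erbai drink granules and Gegen Qinlian decoction granules), children aged ≥ 6 months to ≤ 1 year old: 3/7" of a pack per dose, continuing with 1/2 pack (over 1 to 3 years), 3/4 pack (over 3 to 5 years) and 1 pack (over 5 to 14 years).

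The control-group item ends with the antibiotic rule: "Relevant antibiotics (ceftriaxone sodium for injection: 50 mg/kg/day, single intravenous infusion) can be added if required during the course of the illness", followed by a list of clinical and laboratory signs. Antibiotic use rate is one of two primary outcomes, and the time until antibiotics are started is a secondary outcome.

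**The concern.** A double-dummy design hides allocation only if every child in an age band takes the same amount of each product, whichever of the two is active. Here the age fractions are printed for the placebos and not for the active granules. If sites followed the text literally, a parent or clinician could read the allocation from the packs used per dose.

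This matters more than usual because one primary outcome is a treatment decision. Antibiotics may be added if required, on signs that leave room for judgement. A clinician who can tell that a child is on placebo may add them sooner. The plan itself treats unblinding as serious: a broken blind is among the reasons for a child to leave the trial, and leakage of the blind is given as an example under Suspension criteria.

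**Working it through.** **Inputs**, all from Test drugs except the age range (6 months to 14 years, Selection criteria):

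- Active granules: three packs taken in three doses, so 3/3 = 1 pack per dose, with no age fraction attached.
- Placebo fraction f per dose: 3/7, 1/2, 3/4 or 1, by age band, three times a day.

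**Formulas.** Either experimental arm takes one active plus one placebo product, so 1 + f packs per dose. Control takes two placebos, so 2f. The gap is (1 + f) − 2f = 1 − f, which vanishes only when f = 1. The active-to-placebo ratio within an experimental arm is 1/f.

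| Age band | f | Experimental arm, 1 + f | Control, 2f | Gap, 1 − f | Ratio, 1/f |
|---|---|---|---|---|---|
| 6 months to 1 year | 3/7 | 1.43 | 0.86 | 0.57 | 2.33 |
| over 1 to 3 years | 1/2 | 1.50 | 1.00 | 0.50 | 2.00 |
| over 3 to 5 years | 3/4 | 1.75 | 1.50 | 0.25 | 1.33 |
| over 5 to 14 years | 1 | 2.00 | 2.00 | 0 | 1.00 |

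Per day (three doses) the counts are 4.29 against 2.57, 4.50 against 3.00, 5.25 against 4.50, and 6.00 against 6.00.

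**What the pattern reveals.** Up to age 5, one whole pack and one part pack means an experimental arm; two part packs means control. If the two products can be told apart, the one taken whole is the active one, so the two experimental arms separate as well.

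**Sample size.** The planned 37 per group is not affected. With 46% against 80%, two-sided alpha 0.05 and the printed β of 0.80 read as power, the usual formula gives 31 per group without continuity correction and 37 with it, which reproduces the plan's figure. Nothing in it depends on the pack schedule.

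**Antibiotic sentence.** It is printed at the end of the control-group item but names no arm. Study aim describes the two preparations "combined with antibiotics as intervention methods to evaluate the clinical efficacy of TCM", and Sample size plans on 46% antibiotic use in the groups given traditional medicine. Both presuppose antibiotic use in the experimental arms.

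**The case against.** The best defence is that the age bands were meant for active and placebo alike. The active entries may describe only composition and how the granules are packed, while the schedule is written once, next to the placebo. Matched taste and packaging and the stated double-blind design point that way. On this view age scaling of the active granules is simply unstated, and no second active schedule exists to contradict the first. That is plausible, and it means that actual unblinding has not been shown. But the text does not say it, and three packs in three doses would then describe only children over 5. Nor is this a detail lost in condensing: the article prints the schedule for each arm, and the printed arms do not match.

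Several stronger readings are tempting and are not supported:

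- *Antibiotics are allowed in control only, so use in the experimental arms is 0% by rule and the endpoint fails.* The sentence closes a run-together list and does not restrict itself to control. The aim, the outcomes and the 46% planning rate all rule this reading out. What remains is an ambiguous position on the page.
- *The antibiotic signs repeat the entry criteria, so children qualify on day 0.* Entry may indeed rest on stool white cells "or increased procalcitonin, percentage of CRP or neutrophils, or total number of white blood cells in routine blood", and several of these markers recur in the antibiotic rule. But that rule applies during the illness and sits beside rising stool frequency and lack of improvement, so it is most naturally read as change after entry. Any overlap at baseline would be balanced by randomization in expectation; it could dilute a difference but would not by itself create one. This is at most loose wording, and it gives no ground to require that the signs differ from the entry criteria.
- *The blind fails for the whole trial.* Above age 5 the counts are equal in all arms.

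**Conclusion.** The point holds for children aged 5 or under. As printed, Test drugs gives them different pack counts by arm, with a gap of 0.57, 0.50 and 0.25 packs per dose in the three younger bands and none above 5 years. That is incompatible with a double-blind, double-dummy comparison in those bands, and it exposes a discretionary primary outcome to bias.

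The conclusion rests on three assumptions: that three packs in three doses means one pack per dose, three doses a day; that sites dispense as the text reads; and, for telling the two experimental arms apart, that the products can be distinguished. The article gives no age distribution, so the share of the 120 children affected is unknown. It ranges from none, if all are over 5 or the bands were applied to every product, to all, if every child is 5 or under and the text is followed literally. The position of the antibiotic sentence is a minor matter of clarity.

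**What to change.** Reconcile Test drugs so that, in each age band, the packs per dose are stated identically for each active product and its matching placebo in all three arms. Which schedule is right is for the clinical team. Then check what the sites have in fact dispensed, by age band. Recruitment was under way at submission and planned to run to 31 December 2021. If packs did differ by arm, the lost blinding cannot be restored later, and the trial report would have to say so.

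As a minor clarification, give the antibiotic sentence its own paragraph and state that it covers all three arms, in line with Study aim and Sample size.

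The cost is a clarifying amendment, a memo to the three centers and a dispensing check. The sample size does not change.

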**Methods:**

This randomized, double-blind, placebo-controlled clinical trial has completed ChiCTR registration. The trial will randomly divide 120 children who meet the inclusion criteria into three groups: experimental group 1 (basic treatment + Gegen Qinlian decoction granules + Erbai drink placebo), experimental group 2 (basic treatment + Erbai drink granules + Gegen Qinlian decoction placebo), and control group (basic treatment + Gegen Qinlian decoction placebo + Erbai drink placebo). The main efficacy indicators will be antibiotic use rate and clinical cure rate, and the secondary efficacy indicators will be time to antibiotic intervention, effective rate, and course of treatment determined after 5 days. The following physical and chemical indicators will be measured: routine blood parameters, procalcitonin, C-reactive protein, electrocardiogram, liver and kidney function, electrolytes, routine urinalysis, routine stool analysis, and stool culture (including drug sensitivity).

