Erbai drink is an empirical prescription used by the master of traditional Chinese medicine, Wang Lie. This prescription is used to treat diarrhea of damp-heat type in children. However, in the existing guidelines [12], the prescription for pediatric damp-heat diarrhea is Gegen Qinlian Decoction, But, in clinical application, the master of Chinese medicine Wang Lie found that Erbai drink also has a significant effect in the treatment of diarrhea in children with damp-heat type. Wang et al. [13] summarize Wang Lie’s experience and found that Erbai drink is “harmonizing spleen yin and yang, clearing heat, promoting diuresis and detoxifying,” which is used to treat diarrhea in children with damp heat.

Erbai drink granules: Radix Paeoniae Alba (Bai Shao) 10 g, Rhizoma Atractylodis Macrocephalae (Bai Zhu)10 g, Radix scutellariae (Huang Qin) 10 g, Semen Coicis (Yi Yiren ) 10 g, Rhizoma Atractylodis (Cang Zhu) 5 g, Semen Plantaginis (Che Qianzi)10 g; Gegen Qinlian decoction granules: Radix Puerariae lobatae (Ge Gen) 10 g, Radix Scutellariae (Huang Qin) 10 g, Rhizoma Coptidis (Huang Lian) 5 g, Radix Glycyrrhizae (Gan Cao) 5 g. Two Chinese medicine prescriptions can all clear away heat, eliminate dampness ,and stop diarrhea for children with damp-heat diarrhea, but it can be found from the composition of the medicine that Gegen Qinlian decoction has a better heat-clearing effect and Erbai drink has a better dampness-eliminating effect. So, we hope that this difference can be verified in actual clinical observations.

Therefore, it is necessary to implement clinical trials to determine the safety and efficacy of TCM (Gegen Qinlian decoction and Erbai drink) in the treatment of antibiotic-resistant bacterial diarrhea in children.

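### The age-banded pack fractions are printed only for the placebos, so each active and its matching placebo carry different dosing rules; probably a drafting slip, but the text needs correcting and the dose actually used needs checking

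*Protocol article*

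**What the plan says.** In the protocol article, Interventions, Test drugs, the entry for experimental group 1 lists the Gegen Qinlian herbs in grams as a child's dose and continues: "divided into three packets), orally in three times. Placebo (same taste and packaging as Erbai drink granules), children aged". The four age bands follow. Experimental group 2 has the same structure for Erbai: "divided into three packs) orally in three times. Placebo (taste and packaging same as Gegen Qinlian decoction granules), children aged", again followed by the bands. The control group has one band list for two products: "placebo (taste and packaging same as Erbai drink granules and Gegen Qinlian decoction granules), children aged".

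The bands are the same in every arm. Three times a day, the child takes 3/7 pack from 6 months to 1 year, 1/2 pack above 1 to 3 years, 3/4 pack above 3 to 5 years, and 1 pack above 5 to 14 years. No sentence in the article attaches them to an active product.

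Three other statements bear on the point:
- Selection criteria: "Age from 6 months to 14 years", so all four bands can be enrolled.
- Interventions, on duration: "One course of treatment for the above three groups will last 5 days, and one to two courses can be administered continuously".
- Abstract, Methods: each arm receives two products, for example "experimental group 1 (basic treatment + Gegen Qinlian decoction granules + Erbai drink placebo".

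**The concern.** Every arm takes two products, so that a child on one active also takes the placebo of the other. This hides allocation only if an active and its own placebo are taken in the same amount at every age. As printed they are not, except above 5 years.

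Two things would be at stake if the text were followed as it stands. The first is safety: the youngest children would take the active with no age reduction. The second is blinding: a child aged 5 or under in a herbal arm would take a whole packet of one product beside a fraction of the other, while a control child would take two equal fractions. Matching taste and packaging would not hide that. Blinding matters here because antibiotic use is a primary outcome and the decision to add ceftriaxone rests partly on judgement. The listed triggers include "a lack of improvement in stool characteristics, fever, increased proportion of neutrophils in the blood, increased CRP or procalcitonin", which mixes an assessed sign with laboratory measures.

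**Working it through.** The article reports no calculated figure on this point. The inputs are its pack fractions and herb weights. The sample size does not enter.

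**Inputs (Test drugs section)**
- Fraction per dose, f = 3/7, 1/2, 3/4, 1 for the four age bands; three doses a day.
- Active: three packets, one per dose, no age rule.
- Herb weight in the three packets: Gegen Qinlian 10 + 10 + 5 + 5 = 30 g; Erbai 10 + 10 + 10 + 10 + 5 + 10 = 55 g.
- Assumption for the literal reading: the child's dose is one day's supply. The active text does not say per day.

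**Literal reading (bands for placebos only)**
- Active packs per day = 3; accompanying placebo = 3f.
- Herbal arm total = 3 + 3f; control total = 3f + 3f = 6f.
- Active relative to the banded dose = 3 / 3f = 1/f.

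**Intended reading (bands for all granules)**
- Every product = 3f packs per day; every arm = 6f; difference between arms = 0.

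| | 6 months to 1 y | >1 to 3 y | >3 to 5 y | >5 to 14 y |
|---|---|---|---|---|
| f | 3/7 | 1/2 | 3/4 | 1 |
| Literal: active, packs/day | 3 | 3 | 3 | 3 |
| Literal: its companion placebo, packs/day | 1.29 | 1.50 | 2.25 | 3 |
| Literal: herbal arm total, packs/day | 4.29 | 4.50 | 5.25 | 6 |
| Literal: control total, packs/day | 2.57 | 3.00 | 4.50 | 6 |
| Active, literal / banded (1/f) | 2.33 | 2.00 | 1.33 | 1.00 |
| Gegen Qinlian, g/day, literal | 30 | 30 | 30 | 30 |
| Gegen Qinlian, g/day, banded (30f) | 12.9 | 15 | 22.5 | 30 |
| Erbai, g/day, literal | 55 | 55 | 55 | 55 |
| Erbai, g/day, banded (55f) | 23.6 | 27.5 | 41.25 | 55 |

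**What would tell the readings apart in records**
- Amount of active taken per dose: 1 pack at every age (literal) against 3/7, 1/2, 3/4 or 1 (banded).
- Over one 5-day course: 15 packs taken (literal) against 15f = 6.43, 7.5, 11.25 or 15 (banded).
- Whole packs dispensed may not help. If a fresh pack is opened for each dose and the remainder discarded, 3 × 5 = 15 packs are used under both readings.

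**The case against.** The strongest reply is that the herb text only defines what one pack contains, and the bands then say how much of a pack to take, for any product. Much supports this:
- A pack fraction means nothing until a pack is defined, and for the actives that definition is in the herb list.
- The Background prints the same list simply as composition: "Gegen Qinlian decoction granules: Radix Puerariae lobatae (Ge Gen) 10 g, Radix Scutellariae (Huang Qin) 10 g, Rhizoma Coptidis (Huang Lian) 5 g".
- The control arm's one band list already serves two products.
- The top band, 1 pack three times, equals the three packets.
- The active text has no per-day wording, so even the literal reading needs an added assumption.
- Giving each arm one product and the other's placebo makes sense only with equal amounts.

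The article also condenses a fuller protocol, where dispensing instructions would normally sit, so staff may never have dosed from this paragraph.

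Most of this stands, and it makes a drafting slip the likelier reading. It does not make the printed text right. The article goes into dosing detail and attaches the bands to the placebos alone, in all three arms. That is a misplaced rule, not a detail left to another document.

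A reader might go further and infer that infants are being overdosed, or that the blind is broken. The documents do not support either: they do not show that anyone followed the literal text. Nor would unequal amounts by themselves reveal which herbal product a child received. That also requires the two products to be distinguishable, which the article does not say.

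**Conclusion.** The point holds as a wrongly stated dosing rule with a possible, unproven consequence. If the bands were meant for all granules, which is more likely, the difference between arms is zero and only the wording is at fault. If the literal text was used and the child's dose is one day's supply, children aged 5 or under took 1.33 to 2.33 times the banded dose of active, and pack amounts separated herbal treatment from control. Children over 5 are unaffected under either reading.

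The size of any resulting bias in antibiotic use or cure cannot be computed. The age mix is not given, and several antibiotic triggers are laboratory measures that knowledge of allocation would not change. The point still merits action: the trial enrols from 6 months, treatment may run to two courses, and the Trial status section says recruitment was under way.

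**What to change.** State one pack rule per age band, once, and say that it applies identically to each active and its matching placebo in all three arms. The clinical team chooses the rule.

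Then confirm that this rule was used, from the amount taken per dose in the patient diary described under Drug control. Do not rely on counts of whole packs dispensed. The article does not say whether the diary records part packs; if it does not, the dosing instructions given to families are the next place to look.

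If the bands were applied to all products, correct the text and do nothing else. Only if the literal rule was used, report adverse events by age band and disclose the possible unblinding in children aged 5 or under. An efficacy analysis restricted to children over 5 is not recommended, because the subgroup's size is unknown and its interval would probably be too wide to inform.

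Cost: one sentence of text and a diary check, plus one safety table and a disclosure in the worse case. No extra patients or procedures are needed, and sample size, power and alpha are unchanged.
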